### Process evaluation

Process evaluation will be completed by parents and GPs. The items will document extent to which interventions were implemented, acceptability, barriers to attendance, and perceived harms and benefits. Parents will report other assistance received (source, type, intensity) for their children’s weight status.

### Economic evaluation

If the intervention is effective, we will proceed to a full economic evaluation. This will comprise !analysis conducted from both societal and health care perspectives [34], as interventions cost-effective from a health care perspective can add substantially to family costs [35]. This will compare any incremental costs of the intervention (over the control group) to all incremental outcomes detailed above. Resources used in intervention design, development and delivery have been prospectively documented via research team records, the trial database, hospital and general practice records, and parental report and valued using existing unit cost estimates. Uncertainty in the cost and outcome data and sensitivity of results to the evaluation methods chosen will be tested through extensive sensitivity analyses.

### Sample size

The target sample size was calculated to detect a mean difference of 0.3 BMI z-score units at 15 months (comparable to published mean changes seen from specialist obesity clinics[4]) between arms with 80% power at 5% (2 sided) level of significance. Allowing for 10% loss to follow-up, we aimed to recruit 172 children.

### Data Analysis

Analyses will be by ‘intention to treat’ at the level of the individual child. Linear regression will be used to compare quantitative outcomes between the trial groups adjusting for confounders and baseline measures of the outcomes where these are available, using an analysis of covariance approach. Logistic regression will be used to compare dichotomous outcomes.

Confounders selected *a priori* for multivariable models will include child sex, age at randomisation, and family socioeconomic status, which will be assigned according to postal code of residence using the Index of Relative Socioeconomic Disadvantage (mean 1000, s.d. 100) from the Australian Bureau of Statistics census-based Socio-Economic Indexes for Areas (SEIFA) [36].

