### GP recruitment and training

To recruit GPs, HopSCOTCH was widely advertised through the Royal Australian College of General Practitioners and the Victorian general practice research network ‘VicReN’ e-bulletins/newsletters. Personalised invitations were also sent to GPs who previously participated in the LEAP 1 and LEAP 2 trials [10,29]. Of the 70 GPs who initially expressed interest, 35 GPs across 22 practices decided to take part.

GPs attended a 2½ hour group training session for instruction in the “stages of change” model [30] and training in brief, solution-focused family therapy [31]. GPs were shown role model scenarios of GPs using solution-focused therapy in consultations for healthy family lifestyle and given the opportunity to mimic these skills themselves with colleagues in role play scenarios designed by the research team. GPs also completed readings on current obesity management, followed by a brief online quiz to test their knowledge and training in measuring protocols. Those delivering the intervention received one-on-one training in how to use the specially designed shared-care software. GPs were provided with the following remuneration for their time and for bulk-billing all shared-care patients: $220 for attending the training sessions; $25 per child recruited from their practice; and $75 for GPs that saw shared-care patients five times and an additional $75 if they saw them eight or more times.

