#### *Randomisation and blinding*

Randomisation occurred via a concealed, computerised random number sequence stratified by general practitioner and pre-generated by the Clinical Epidemiology and Biostatistics Unit at the Royal Children’s Hospital. Once enrolled (i.e. on receipt of written informed consent and baseline questionnaire) a research assistant, who was not otherwise involved with the trial, randomised children to either the shared-care or usual-care arm. All families were advised of their child’s allocation by a mailed letter. All outcome measures were collected by researchers blinded to the child’s allocation status.

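### Allocation is stratified by GP but the stated model has no GP term; if allocation was balanced within GP, a little precision is lost, which a GP random intercept would largely recover

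*Protocol article*

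**What the plan says.** Three places in the protocol article bear on this.

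- **Randomisation and blinding:** allocation came from a "computerised random number sequence stratified by general practitioner". Block size and allocation ratio are not given.
- **GP recruitment and training:** the strata are numerous, since "35 GPs across 22 practices decided to take part".
- **Data Analysis:** the analysis is by intention to treat "at the level of the individual child". Quantitative outcomes are compared by linear regression "adjusting for confounders and baseline measures of the outcomes where these are available, using an analysis of covariance approach", and dichotomous outcomes by logistic regression. The confounders chosen in advance "will include child sex, age at randomisation, and family socioeconomic status".

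No GP or practice term, random effect, stratified analysis or cluster-robust standard error is mentioned.

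**The concern.** An analysis should normally reflect the factor that restricted the randomisation. Balancing the arms within each GP removes between-GP differences from the treatment contrast. A model without GP still counts those differences as residual noise, so the reported standard error exceeds the true sampling error. The p-value is then slightly too large and the confidence interval slightly too wide.

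Within-GP correlation is plausible here, because children of one GP share a practice and often a neighbourhood. Area socioeconomic status by postcode would absorb only part of that. The article does more than stay silent: it fixes the regression type, the unit of analysis and a named covariate list. A reader applying it as written would fit a model without GP. What is at stake is some efficiency, not validity.

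**Working it through.** **Inputs from the article.** The target is to "detect a mean difference of 0.3 BMI z-score units at 15 months" with 80% power at two-sided 5%, 10% loss to follow-up and 172 children (Sample size). The Participants section gives 120 children. There are 35 GPs.

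**Assumed.** 1:1 allocation, and an ICC between 0.01 and 0.10.

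**The plan's own figure.** The article gives no SD, so 172 cannot be reproduced from its inputs. Back-solving with 172 × 0.9 = 154.8 analysed (77.4 per arm):

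SD = 0.3 / [(1.960 + 0.842) × sqrt(2/77.4)] = 0.666

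With 77 per arm it is 0.664, the value used below. The conclusion does not depend on it.

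**Stratum size.** 120/35 = 3.4 or 172/35 = 4.9 children per GP.

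**Standard error without GP.**
- 155 analysed: 0.664 × sqrt(2/77.4) = 0.1067, and 0.3/0.1067 = 2.81.
- 108 analysed (120 × 0.9): 0.664 × sqrt(2/54) = 0.1278, and 0.3/0.1278 = 2.35.

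**Effect of omitting GP under full balance within GP.** Let f = sqrt(1-ICC) and z = 0.3/SE. The true standard error is f times the reported one. Then:
- type I error without GP = 2 × [1 - Φ(1.96/f)]
- power without GP = Φ[(z - 1.96)/f]
- power with GP = Φ(z/f - 1.96)

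| ICC | SE too large by | Type I without GP | Power, 155: without / with GP | Power, 108: without / with GP |
|---|---|---|---|---|
| 0 | 0% | 0.050 | 80.3% / 80.3% | 65.1% / 65.1% |
| 0.01 | 0.5% | 0.049 | 80.4% / 80.6% | 65.2% / 65.5% |
| 0.05 | 2.6% | 0.044 | 80.9% / 82.2% | 65.5% / 67.3% |
| 0.10 | 5.4% | 0.039 | 81.5% / 84.2% | 65.9% / 69.7% |

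Full balance is the ideal case. With three to five children per GP many blocks stay incomplete, so the real effect is somewhat smaller.

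**Simulation** (35 GPs of unequal size, 2,000 replicates per setting, ICC treated as known):
- *Blocks of 4, 155 analysed, ICC 0.10.* Without GP the mean reported SE was 0.106 against an empirical SD of 0.101, type I error was 0.037 and power 80.8%. A random intercept gave mean SE 0.102 and power 83.4%. GP fixed effects gave 81.2%.
- *Blocks of 4, 108 analysed, ICC 0.05.* Power was 65.8% without GP, 66.8% with a random intercept and 60.7% with fixed effects. Dummies can therefore cost more than they gain.
- *No blocking, 155 analysed.* Type I error without GP was 0.049 to 0.054 across ICC 0.01 to 0.10, so there was no clear conservatism.

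**With the ICC estimated** (108 analysed, ICC 0.05), the random intercept moved power from about 68% to 69% with blocks and from about 63% to 64% without. Type I error stayed near 5% throughout.

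**The case against.** **The covariate list is not closed.** It names confounders, a stratification factor is not one, and the wording is not exhaustive. Analysing by individual child does not exclude a GP random effect, and a condensed article may leave this to an analysis plan. This stands in part: the point concerns the model as written, and the trial may already intend a GP term.

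**Blocking is not stated.** This stands. The excess standard error follows only if the arms are balanced within GP. A reader might infer that the planned test is certainly conservative; the article does not support that.

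**The gain is small.** This stands. The relevant ICC is what remains after adjustment for baseline and area socioeconomic status, which may absorb part of the between-GP variation. In simulation with a true ICC of 0.05 and about three children per GP, the ICC was estimated at zero in about 35 to 40% of replicates. Large gains would need an ICC well above 0.10, and nothing in the article supports one. The low power at 108 analysed comes from the difference between 120 and 172 children, which is a separate matter.

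**GP effects may sit in one arm only.** GPs deliver the programme to intervention children, and the Control arm section says control children are not identified to their GP as trial participants. With GP effects confined to the intervention arm (0.20 of that arm's variance, 108 analysed, blocks of 4), simulated type I error was 0.073 without GP and 0.082 with a random intercept. The direction reverses there, and the random intercept does not repair it. This is a different mechanism. It does not remove the component shared by both arms, which is what stratification targets, but it means that delivery by the GP should not be used to argue for the random intercept.

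**A stronger reading to avoid.** A reader might infer that ignoring GP inflates false positives, as it would in a cluster-randomised trial. The article describes children randomised individually within GP strata, so omitting the shared GP component has no such effect.

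**Conclusion.** The point holds in a limited, conditional form. The randomisation and analysis sections do not match: allocation is stratified by GP, and the stated model has no term for it. Given balance within GP and an assumed ICC of 0.01 to 0.10, the reported standard error is too large by up to about 5%, and type I error falls to between 0.049 and 0.039. Roughly 0.2 to 4 power points are given up. Without blocking there is little or no conservatism, and at an ICC of zero there is no loss. The omission creates no bias in the treatment effect and does not invalidate the planned analysis. It is worth correcting because the correction is nearly free.

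**What to change.** - **Linear models** (primary and other quantitative outcomes): add GP as a random intercept. Do not use 34 GP dummies, which can lose power at three to five children per GP.
- **Binary outcomes:** prespecify one approach. GEE clustered by GP with a small-sample correction, for example, keeps the marginal odds ratio. A random-intercept logistic model targets a conditional one, so the two are not interchangeable.
- **Reporting:** state whether allocation was blocked within GP, so that readers can judge how much the term matters.

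The cost is one extra variance parameter and no new data. That variance will often be estimated at zero, in which case the linear model reverts to the planned one.

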## Aims and hypothesises

The **aim of the HopSCOTCH trial** is to develop, implement and trial an innovative shared-care approach to manage childhood obesity. We will compare outcomes for 3–10 year old obese children randomised to a shared-care model (general practitioners working with paediatric obesity specialist, consisting of a paediatrician and dietician - ‘intervention’ group) with outcomes for those receiving usual patient-driven primary care (‘control’ group).

We **hypothesise** that:

1. Compared to the control group, the intervention children will demonstrate better outcomes at 15 months in terms of lower:

i) Relative BMI, measured as a z-score (primary outcome)

ii) Percentage body fat

iii) Waist circumference

2. Compared to the control group, the intervention children will not show evidence of harm (ie poorer health status, body satisfaction, or global self-worth) at 15 months.

3. The intervention will be acceptable and feasible to (i) parents, (ii) general practitioners, (iii) general practice staff, and (iv) the obesity specialists.

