### Recruitment of children

To recruit children, HopSCOTCH was publicised in participating practices through posters, brochures and practice staff. Trained general practice staff opportunistically offered to weigh and measure children using calibrated digital scales and rigid stadiometers supplied by the research team. Eleven practices also sent letters to all of their in-age children inviting them to attend a dedicated weigh and measure session run by the research team or practice staff at the practice. With parent assent, their contact details and child anthropometry data were then mailed or faxed to the research team. Upon receipt, the research team calculated each child’s BMI and BMI percentile. Provided parents had left contact details, ineligible children’s families were sent a letter informing them of their ineligibility, while eligible families were telephoned to propose participation in the trial. Interested eligible families were mailed a parent information sheet, consent form and parent baseline questionnaire. Upon receipt of the written informed consent and the parent baseline questionnaire, families were enrolled in the trial.

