**Secondary Outcomes**				
Waist circumference		**•**	Lufkin Executive Steel Tape (W606PM); measured	Average of two waist measurements; if they differ by ≥1 cm, a third measurement is taken and the mean of the two closest used.
Body fat (%)		**•**	Tanita Digital Body Composition Monitor (BC-351)[37]; measured	Average of two body percentage fat measurements.
Blood pressure/ heart rate		**•**	Welch Allyn ProBP3400; measured	Three blood pressure/heart rate readings are taken at least two minutes apart on the right arm with the child sitting; the average of the two closest readings is used.
Nutrition		**•**	4 day food diary; parent report	Parents report child’s consumption of each of 17 food and drink items (0, 1, 2, >2 times) for two weekdays and two weekend days. Dichotomous (“yes” v “no”) variables are derived for five “healthy behaviours” (high fruit, vegetables, and water; low fatty/sugary foods and non-diet sweet drinks) for each day. The number of healthy behaviours per day are summed to give a score between 0 and 5 (higher score indicating more healthy behaviour).
Physical activity		**•**	Actical Accelerometer (Mini Mitter); measured	Worn for 7 full days; ≥5 valid days required. Valid days have ≥10 hours of non-missing data between 6 am-11 pm. Missing data are segments with ≥20 minutes of consecutive “0” counts, or counts >0 that are constant for ≥10 minutes. Outcomes across all valid days: mean activity counts/min, and % time spent in moderate to vigorous physical activity.
Health status	**•**	**•**	Paediatric quality of life inventory (PedsQL 4.0); self report and parent-proxy versions [38]	Parent-completed 23-item scale that yields total, physical summary, and psychosocial summary scores, each with a possible range of 0–100 (100 = best possible health); quantitative variable.
Body dissatisfaction		**•**	Body figure perception questionnaire; self report [39]	Child picture scale of 1–7 (1 = underweight, 7 = obese) from which child picks perceived and ideal selves. “Perceived” minus “Ideal” self yields a discrepancy index, with positive and negatives scores representing desires to be thinner and fatter, respectively.

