Physical appearance and self worth		**•**	Modified from Harter’s perceived competence scale; self report	Six pairs of statements with binary response format; children choose the statement from each pair that is closest to their competence. Each of the 6 responses is then coded as being either “positive/better perception” or “negative/worse perception”. The 6 responses are analysed as a single outcome.
Behaviour		**•**	Strengths and difficulties questionnaire [40]; self report	Parent-completed 25-item scale that yields scores for conduct problems, emotional symptoms, hyperactivity, peer relationships and pro-social behaviour.
Parent Readiness to change	**•**	**•**	Parent’s readiness to change child’s weight[41]; self report	3 items, each with a possible 5 responses (strongly agree – strongly disagree).
Parent BMI		**•**	Weight (kg)/(height (m)2); measured and self report	Baseline values reported for self and partner by responding parent. Values at 12 months measured for the parent(s) present with the child and reported; measured data used preferentially.

All researchers involved in baseline and outcome measurements were trained by researchers experienced in conducting similar measurements in the community from other research trials and longitudinal studies in childhood obesity. Researchers were trained at a single one-hour session where each measurement was demonstrated and repeatedly practised to ensure accuracy, competency, and reliability.

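### Adjusting only for an outcome's own baseline leaves the baseline PedsQL unused for the SDQ, body dissatisfaction and self-worth: a modest loss of precision, not a bias

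*Protocol article*

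**What the plan says.** The Data Analysis section sets one adjustment rule. Quantitative outcomes are compared by linear regression, "adjusting for confounders and baseline measures of the outcomes where these are available". The confounders chosen in advance "will include child sex, age at randomisation, and family socioeconomic status", the last taken from postcode. For binary outcomes the section says only this: "Logistic regression will be used to compare dichotomous outcomes".

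Hypothesis 2 in the Aims section states that intervention children "will not show evidence of harm (ie poorer health status, body satisfaction, or global self-worth) at 15 months". It gives no margin.

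Table 1 shows which outcomes have a baseline of their own:

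- Health status is marked at baseline and outcome. The measure is given as "Paediatric quality of life inventory (PedsQL 4.0); self report and parent-proxy versions", and the scale yields a psychosocial summary score.
- Body dissatisfaction is marked at outcome only and is reported by the child.
- Physical appearance and self-worth is marked at outcome only. It consists of six two-way choices made by the child and analysed as one outcome.
- Behaviour (SDQ) is marked at outcome only. It is described as a "Parent-completed 25-item scale that yields scores for conduct problems, emotional symptoms, hyperactivity, peer relationships and pro-social behaviour".

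On timing, the Recruitment of children section says: "Upon receipt of the written informed consent and the parent baseline questionnaire, families were enrolled in the trial". Randomisation followed enrolment.

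**The concern.** Two of the three outcomes named in hypothesis 2 (body satisfaction and global self-worth), together with the SDQ, have no baseline of their own. The stated rule therefore gives them only sex, age and area disadvantage as covariates. A related psychosocial score should exist from before randomisation for nearly every child, because the parent questionnaire had to be returned first. The rule makes no use of it.

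Precision is worth having here. A hypothesis of no evidence of harm, stated without a margin, is easier to satisfy when intervals are wide, and the arms are small. A prognostic covariate named in advance narrows the interval at almost no cost. One chosen after the data are seen is open to challenge.

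**Working it through.** **No figure of the plan to reproduce.** The protocol gives no power or precision for these three outcomes. Its target of 172 concerns BMI z-score and is used here only to set the number analysed.

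**Inputs from the protocol.** The Sample size section gives a target of 172 children and 10% loss. The Participants section gives 120 children. Both totals are carried through.

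**Assumptions.**

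- Allocation is 1:1.
- The 10% loss applies to either total.
- r is the correlation of baseline PedsQL psychosocial score with the 15-month outcome, given sex, age and area disadvantage. It is not in the document, so a range is shown.
- The outcome is analysed by linear regression. SD means the residual SD after the existing covariates.

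**Number analysed per arm, m.** 172 × 0.9 / 2 = 77.4, and 120 × 0.9 / 2 = 54.

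**Formula.** Adding the covariate multiplies the residual variance by (1 − r²). In SD units, the 95% half-width is 1.96 × √(1 − r²) × √(2/m). Relative narrowing is 1 − √(1 − r²), which does not depend on m. The equivalent gain in sample size is 1/(1 − r²) − 1.

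**Without the covariate.** 1.96 × √(2/77.4) = 0.315 SD, and 1.96 × √(2/54) = 0.377 SD.

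**With the covariate.**

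| r | Interval narrower by | Equivalent gain in N | Half-width, m = 77.4 | Half-width, m = 54 |
|---|---|---|---|---|
| 0.1 | 0.5% | 1% | 0.313 | 0.375 |
| 0.2 | 2.0% | 4% | 0.309 | 0.370 |
| 0.3 | 4.6% | 10% | 0.301 | 0.360 |
| 0.4 | 8.3% | 19% | 0.289 | 0.346 |
| 0.5 | 13.4% | 33% | 0.273 | 0.327 |
| 0.6 | 20.0% | 56% | 0.252 | 0.302 |

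The smallest difference detectable with 80% power (two-sided 5%) is (1.96 + 0.84) × √(1 − r²) × √(2/m). At m = 77.4 it falls from 0.450 SD to 0.430 SD at r = 0.3 and 0.390 SD at r = 0.5. At m = 54 it falls from 0.539 SD to 0.514 SD and 0.467 SD.

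**Which part of the range is likely?** The baseline instrument was a questionnaire for parents, and Table 1 describes the PedsQL as completed by the parent. The baseline score is therefore probably the parent-proxy version. Table 1's description of the SDQ also makes the parent its informant (although its measure column says self report), so a moderate r is plausible there. Body dissatisfaction and self-worth are reported by the child, 15 months later, on different constructs, so a low r is plausible. This is inference; the document gives no correlation.

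**Where the formula may not fit.** If the six binary self-worth items go into a logistic model, the (1 − r²) factor does not carry over directly, and adding a prognostic covariate also changes the odds ratio being estimated. Body dissatisfaction is a signed discrepancy, so a linear relation with PedsQL is not assured.

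**The case against.** The strongest reply is that nothing here is wrong. Adjusting for an outcome's own baseline plus covariates chosen in advance is a valid rule, and borrowing another scale as covariate is a refinement. The confounder list is not expressly closed, and an analysis plan that is not shown could add the covariate. This stands, and it is why the point is optional. What remains is that the rule as written does not provide for the covariate.

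A reader might infer that the harm comparisons are biased, or that chance imbalance at baseline is a second problem beside the wide intervals. The document supports neither. Randomisation keeps the comparison unbiased, and the unadjusted interval already allows for chance imbalance. Imbalance and width are one loss of precision, not two.

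A reader might also infer that the no-harm answer as a whole is materially weakened. That goes too far. Health status has its own baseline and is already adjusted for it. The SDQ, the likeliest to gain, is not named in hypothesis 2 and bears on it only indirectly. For the two named outcomes that are affected, the gain is unquantified and probably small.

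Two further objections stand in part. Table 1's baseline marks may be incomplete: parent BMI is marked at outcome only, yet its own note says baseline values were reported. If the SDQ was in the baseline questionnaire, the present rule already covers it. The choice of covariate is also a judgement; for body dissatisfaction, baseline BMI is an arguable alternative.

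**Conclusion.** The point holds as an unused gain in precision, of low severity. As written, the rule adjusts the SDQ, body dissatisfaction and self-worth for no baseline psychosocial measure, although Table 1 indicates that the trial holds one. The estimates remain valid.

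Under linear regression the relative loss of precision is the same whichever total is taken, and it turns on r alone: negligible to slight up to 0.3, worthwhile from about 0.4. The upper range is more plausible for the SDQ than for the two child-reported scales, and for self-worth the calculation may not apply at all. The conclusion rests on Table 1's marks being complete for these three rows and on the baseline PedsQL being the parent-proxy version.

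**What to change.** Add to Data Analysis, before unblinded analysis: *SDQ scores with no baseline of their own will be adjusted for the baseline parent-proxy PedsQL psychosocial summary score. The same covariate will be added for body dissatisfaction and for physical appearance and self-worth. The existing covariates are kept.*

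First check the baseline questionnaire. If it contains any of these three scales, that scale's own baseline should be used.

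The cost is a sentence or two of wording, one degree of freedom per model and some item non-response on the baseline PedsQL. With 2 × 54 = 108 children analysed, the degree of freedom costs roughly 1/108, or 0.9%, of variance, about what r = 0.1 gives back (0.1² = 1%). Non-response matters more: at r = 0.2 the gain is worth about 4% more children, so dropping about 4% for a missing baseline score would cancel it. The text should therefore say how a missing baseline value is handled, so that no child leaves the comparison for that reason.
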